### Composition of the data monitoring committee, its role and reporting structure {21a}

Data monitoring is performed to ensure that all events (i.e. PROMS, radiology) are performed according to the study protocol. The data monitoring committee consists of the chief investigator ([name], Prof., MD, PhD) and researchers ([name], MD, PhD, and [name], MD, PhD). Other investigators are responsible for recruitment, data collection, adherence to study protocol: [name], MD, [name], MD, PhD, [name], MD, [name], MD, PhD)

### Adverse event reporting and harms {22}

Potentially analysed adverse events (AE) include implant failure, infection, neurologic deterioration after surgery, and other implant- or approach-related complications. Other AEs are not considered, including pulmonary embolism due to deep vein thrombosis, sepsis, meningitis, severe heart failure, etc. All AEs are reported directly to the chief investigator.

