## Statistical methods

### Statistical methods for primary and secondary outcomes {20a}

The results will be analysed using the intention-to-treat principle. Statistical significance will be defined as *p* < 0.05 based on a two-sided test. No adjustments for multiple tests are planned. The normality of variables will be evaluated using the Shapiro-Wilk statistic. Student’s *t*-test (for normally distributed data) and Pearson’s chi-square test (for categorical data) will be used to reveal differences in symptom rates among the groups. Multiple linear regression will be used to measure point estimates and confidence intervals for group differences in the ODI and clinical scale scores from baseline to the 2-year follow-up.

The non-parametric Mann-Whitney *U* test will be used to reveal differences in continuous variables between groups both pre- and postoperatively. Continuous data within the groups will be compared using the Wilcoxon test. Categorical parameters among the groups will be compared using Fisher’s exact two-tailed test.

Complication incidence during the 2-year follow-up will be compared between groups using Kaplan–Meier survival curves and the log-rank test. The significance of the risk factors (predictors) for all registered complications will be evaluated using univariate and multivariate logistic regression models.

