### Interim analyses {21b}

Interim analysis of the obtained follow-up data will be available by 12 months postoperatively for at least 20 patients in each cohort. The criteria for study termination include the following: (1) the number of repeated surgeries in any group exceeds 50%, (2) any group demonstrates a higher frequency of negative neurological postoperative outcomes and/or significant decline of ODI level compared to baseline by at least 10 points, and (3) the number of postoperative complications exceeding 50% in any group.

An interim analysis will be performed by an investigator not involved in patient treatment ([name], MD, PhD).

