## Discussion

Currently, the selection of surgical solutions for lumbar stenosis remains controversial. This study was designed to provide surgeons with high-level evidence by comparing the clinical outcomes of the two most popular treatment methods. The non-inferiority study design [14] was chosen because according to the current evidence [4, 5] and our experience, both methods are non-inferior (comparable) in terms of the primary endpoint, while there may be superiority in certain secondary endpoints, such as cost effectiveness and lower complication rates.

The non-inferior margin was chosen based on the minimum clinically important difference (MCID), which represents the smallest improvement considered worthwhile by a patient. For patients with lumbar spine stenosis, the MCID in ODI score ranges from 12.54 to 12.8 points [15, 16]. Therefore, a non-inferiority margin of *δ* = 12 was selected according to this data.

To develop the structure of this study, we did our best to maximise the homogeneity of the participant groups. For this purpose, we used precise inclusion and exclusion criteria and accurately restricted the range of surgical methods and postoperative rehabilitation treatment. The key role of postoperative rehabilitation in favourable clinical outcomes is widely known. In our study, all included participants are scheduled for rehabilitation treatment at the same rehabilitation centre within 3 months postoperatively. We believe that these conditions maximise the homogeneity of the participant groups and limit possible clinical outcomes by several factors. We suggest that the mentioned structure of the study implicates decompressive intervention as the only factor for favourable clinical outcomes compared to spinal fusion.

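### The harms section counts infection but sets aside sepsis, meningitis, pulmonary embolism and severe heart failure, so on its natural reading the between-group complication comparison omits serious systemic events

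*Protocol article*

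**What the plan says.** The section Adverse event reporting and harms {22} makes three statements in sequence.

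- What may be analysed: "Potentially analysed adverse events (AE) include implant failure, infection, neurologic deterioration after surgery, and other implant- or approach-related complications".
- What is left out: "Other AEs are not considered, including pulmonary embolism due to deep vein thrombosis, sepsis, meningitis, severe heart failure, etc".
- The reporting route: "All AEs are reported directly to the chief investigator".

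Complications are then used in several places, none of which defines the term.

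- Statistical methods {20a}: "Complication incidence during the 2-year follow-up will be compared between groups using Kaplan–Meier survival curves and the log-rank test". The next sentence adds: "The significance of the risk factors (predictors) for all registered complications will be evaluated using univariate and multivariate logistic regression models".
- Interim analyses {21b}, third termination criterion: "the number of postoperative complications exceeding 50% in any group".
- Secondary endpoints: the cost of treating postoperative complications enters the two-year costing, with no exclusion stated.
- Table 2: a row for complications and repeat surgery is ticked for the inpatient stay and for each visit at 3, 6, 12 and 24 months.

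The Discussion explains why complications matter to the argument. It expects the two methods to be comparable on the primary endpoint and adds that "there may be superiority in certain secondary endpoints, such as cost effectiveness and lower complication rates". The Background section likewise lists fewer complications, with shorter stay and lower cost, as grounds for choosing decompression if it proves non-inferior.

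**The concern.** This is a stated rule, so a fuller document could not supply what is absent; it could only contradict the rule. Two things are wrong with it.

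First, it is inconsistent. Infection counts, but sepsis and meningitis do not. A wound infection that progresses to sepsis falls on both sides of the line. Because the list of exclusions is open-ended, other events would have to be classified case by case. The trial is open-label, reports go to the chief investigator, and the chief investigator also sits on the data monitoring committee. That is a poor setting for a discretionary definition of harm.

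Second, the harms section is the only place that says which events are analysed. If it governs the complication comparison, that comparison omits serious systemic events. The counted list is also not neutral between arms: implant-related events can arise only where implants are used, that is, after fusion, whereas the omitted events can arise in either arm. A claim that decompression has fewer complications would rest on a partial count whose bias has no known direction.

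**Working it through.** The protocol states no complication rate and no power for the complication comparison, so there is no figure of its own to reproduce. The check is a comparison of the texts, followed by an illustration of size under assumed rates.

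**1. Texts side by side**

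| Event | Counted list | Excluded list |
|---|---|---|
| Sepsis, meningitis | Yes, as infection; possibly also as approach-related | Yes, by name |
| Pulmonary embolism, severe heart failure | Not named | Yes, by name |
| Neurologic deterioration, implant failure | Yes, by name | No |
| Any other systemic event | Depends on whether it is judged approach-related | Possibly, through the open-ended ending |

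The first row is a direct conflict. The last row has no rule that decides it.

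**2. Events lost from the comparison**

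Inputs: 86 patients, 43 per arm (Sample size {14}). The proportion *p* of patients with an excluded event is an assumption, taken as equal and independent across patients.

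Expected number = 86*p*. Chance of at least one = 1 − (1 − *p*)^86.

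| Assumed *p* | Expected uncounted events | Chance of at least one |
|---|---|---|
| 1% | 0.9 | 58% |
| 2% | 1.7 | 82% |
| 3% | 2.6 | 93% |
| 5% | 4.3 | 99% |

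Each uncounted event is 1/43 = 2.3 percentage points of its arm's complication rate.

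**3. Direction**

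Suppose counted rates of 10% after decompression and 20% after fusion (assumed), and suppose that excluded events fall in patients with no counted complication.

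- Counted events only: difference 10 points, ratio 20/10 = 2.0.
- Add 3 points to each arm: 13% and 23%; difference still 10 points, ratio 23/13 = 1.77. Leaving the events out overstates decompression's relative advantage.
- Add 1 point to decompression and 5 to fusion: 11% and 25%; difference 14 points, ratio 25/11 = 2.27. Leaving them out understates it.

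The protocol gives nothing that would show which case applies.

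**4. Stopping rule**

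The interim look requires at least 20 patients per group at 12 months. With 20, more than 50% means at least 11. I read the criterion as counting patients with a complication. Trigger probability = P(X ≥ 11), X binomial (20, *q*), where *q* is the assumed rate.

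| Counted rate | Counted events only | 3 points added | 5 points added |
|---|---|---|---|
| 20% | 0.0006 | 0.0019 | 0.0039 |
| 30% | 0.017 | 0.035 | 0.053 |

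The criterion seldom fires with or without the excluded events. The other two termination criteria, on repeat surgery and on neurological outcome or ODI, do not use the complication definition.

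**The case against.** The case on the other side has four parts.

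- **Reporting.** All adverse events go to the chief investigator. A reader might infer that the excluded events would never be recorded; the text does not say so. The restriction falls on which events are analysed. This stands, and it makes the correction cheaper.
- **Link between terms.** The harms section speaks of adverse events, while the statistical and interim sections speak of complications. The risk-factor analysis refers to all registered complications, and neither the Table 2 row nor the costing carries an exclusion. A broader reading is therefore possible, and the link is an inference. It remains the natural reading, because no other section defines the term. If the broader reading is intended, the exclusion sentence is misleading and still needs correcting.
- **Scope.** A reader might conclude that the most serious surgical events are all ignored. They are not: neurologic deterioration, implant failure and infection are counted, and repeat surgery is tracked separately. The named exclusions are systemic events.
- **Intent.** The section may mean to count events attributable to implant or approach and to set systemic ones aside. That is a defensible aim for a comparison of techniques. It does not settle where sepsis and meningitis belong, meningitis least of all, and it does not justify leaving the other serious events out of the harms report.

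**Conclusion.** The point holds for the between-group complication comparison and for harms reporting. The rule conflicts with itself on infection, is open-ended, and on the natural reading removes serious systemic events from an analysis that supports part of the trial's rationale. Under assumed rates of 1% to 5%, about 1 to 4 events among 86 patients would be missing, with unknown direction of bias. Those rates are illustrative only.

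A reader might also infer that the safety stopping rule is disabled. The documents do not support that: only the third criterion could be affected, and its 50% threshold is rarely reached whether or not rare events are counted. Nor is the non-inferiority conclusion at risk, since the primary endpoint and the sample size rest on ODI alone. This is a correction to a secondary comparison and to safety reporting, so it should be fixed but does not undermine the main analysis.

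**What to change.** 1. Delete the sentence in the harms section that sets other adverse events aside, and state explicitly how sepsis and meningitis relate to the infection category.
2. Give one definition of complication, and use it in the costing, the statistical methods, the interim criteria and the harms section.
3. Tabulate all serious adverse events by arm through 24 months, whatever their presumed cause, using the existing Table 2 row for collection. Show surgery-related and other events separately, so that the technique-related comparison is not diluted by unrelated events.

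Treatment, visits and sample size do not change. The costs are a little more reporting work and an amendment, since the protocol requires procedural changes to be resubmitted for approval. Recruitment began in April 2022, so events in patients already enrolled may have to be retrieved. Events already reported to the chief investigator should ease that retrieval.

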### Frequency and plans for auditing trial conduct {23}

Study-related monitoring, audits, and inspections of all documents by the trial steering group, the data monitoring committee, and ethics board are planned prior to inclusion of the first patient (baseline), then every 20 inclusions (intermediate) and after the final inclusion (final).

### Plans for communicating important protocol amendments to relevant parties (e.g. trial participants, ethical committees) {25}

All potential changes for the RCT’s protocol will be reported and resubmitted for approval, that is, equal to changes in objectives, endpoints, design, participants population, sample sizes, procedures, or significant administrative aspects.

### Dissemination plans {31a}

Study results will be provided to peer-reviewed neurosurgical and spine surgery journals and presented at international conferences.

## Discussion

Currently, the selection of surgical solutions for lumbar stenosis remains controversial. This study was designed to provide surgeons with high-level evidence by comparing the clinical outcomes of the two most popular treatment methods. The non-inferiority study design [14] was chosen because according to the current evidence [4, 5] and our experience, both methods are non-inferior (comparable) in terms of the primary endpoint, while there may be superiority in certain secondary endpoints, such as cost effectiveness and lower complication rates.

The non-inferior margin was chosen based on the minimum clinically important difference (MCID), which represents the smallest improvement considered worthwhile by a patient. For patients with lumbar spine stenosis, the MCID in ODI score ranges from 12.54 to 12.8 points [15, 16]. Therefore, a non-inferiority margin of *δ* = 12 was selected according to this data.

To develop the structure of this study, we did our best to maximise the homogeneity of the participant groups. For this purpose, we used precise inclusion and exclusion criteria and accurately restricted the range of surgical methods and postoperative rehabilitation treatment. The key role of postoperative rehabilitation in favourable clinical outcomes is widely known. In our study, all included participants are scheduled for rehabilitation treatment at the same rehabilitation centre within 3 months postoperatively. We believe that these conditions maximise the homogeneity of the participant groups and limit possible clinical outcomes by several factors. We suggest that the mentioned structure of the study implicates decompressive intervention as the only factor for favourable clinical outcomes compared to spinal fusion.

In addition to clinical outcomes, we intend to analyse the economic aspects of lumbar stenosis treatment during both in-hospital stay and two postoperative years. Most of the available published studies did not provide any information concerning the cost of treatment and monitoring results. In most developed countries, the cost of treatment may be determined by insurance data and vary significantly. In Russia, all enrolled participants have mandatory medical insurance and implied unified tariffication of all postoperative medical procedures during the 2-year follow-up period. This study might clarify the exact factors, both clinical and financial, to avoid “preventive” fusion in such patients. This can also have a considerable impact on potential outcomes compared with other treatment alternatives

## Trial status

Protocol version: V.2 08.09.2022 Recruiting from April 2022. Approximate date of recruitment completion—December 2024

## Data Availability

All data generated or analysed during the study are included to the published article.

## Abbreviations

ASA: American Society of Anesthesiologists
CPGQ: Chronic Pain Grade Questionnaire
CPCI: Chronic Pain Coping Inventory
CT: Computed tomography
EQ-5D-5L: EuroQol five-dimensional five-level descriptive system questionnaire
Mo: Month
MRI: Magnetic resonance imaging
ODI: Oswestry Disability Index
PCS: Pain Catastrophizing Scale
p/o: Postoperatively
SF-36: Short Form-36 questionnaire
SPIRIT: Standard Protocol Items: Recommendations for Interventional Trials
VAS: Visual analogue scale
